## Abstract

**Background:**

Prophylactic cranial irradiation (PCI) is part of standard care in limited-stage small cell lung cancer (SCLC) at present. As evidence from retrospective studies increases, the benefits of PCI for limited-stage SCLC are being challenged.

**Methods:**

A multicenter, prospective, randomized controlled study was designed. The key inclusion criteria were: histologically or cytologically confirmed small cell carcinoma, age ≥ 18 years, KPS ≥ 80, limited-stage is defined as tumor confined to one side of the chest including ipsilateral hilar, bilateral mediastinum and supraclavicular lymph nodes, patients have received definitive thoracic radiotherapy (regardless of the dose-fractionation of radiotherapy used) and chemotherapy, evaluated as complete remission (CR) of tumor 4–6 weeks after the completion of chemo-radiotherapy. Eligible patients will be randomly assigned to two arms: (1) PCI and brain MRI surveillance arm, receiving PCI (2.5 Gy qd to a total dose of 25 Gy in two weeks) followed by brain MRI surveillance once every three months for two years; (2) brain MRI surveillance alone arm, undergoing brain MRI surveillance once every three months for two years. The primary objective is to compare the 2-year brain metastasis-free survival (BMFS) rates between the two arms. Secondary objectives include 2-year overall survival (OS) rates, intra-cranial failure patterns, 2-year progression-free survival rates and neurotoxicity. In case of brain metastasis (BM) detect during follow-up, stereotactic radiosurgery (SRS) will be recommended if patients meet the eligibility criteria.

**Discussion:**

Based on our post-hoc analysis of a prospective study, we hypothesize that in limited-stage SCLC patients with CR after definitive chemoradiotherapy, and ruling out of BM by MRI, it would be feasible to use brain MRI surveillance and omit PCI in these patients. If BM is detected during follow-up, treatment with SRS or whole brain radiotherapy does not appear to have a detrimental effect on OS. Additionally, this approach may reduce potential neurotoxicity associated with PCI.

## Background

Small cell lung cancer (SCLC) accounts for approximately 15-20% of all cases of bronchopulmonary carcinoma. It is characterized by high malignancy, a tendency to early metastasis. At the time of diagnosis, about one-third of cases are of limited-stage [1]. The standard treatment is chemoradiotherapy for the majority of limited-stage SCLC patients [2].

A meta-analysis showed that prophylactic cranial irradiation (PCI) significantly reduce the incidence of BM by 25.3% compared to the control group (33.3% vs. 58.6%, *P* < 0.001), in patients who achieved complete remission (CR) after chemoradiotherapy, and it also improved the 3-year overall survival (OS) rate by 5.4% (20.7% vs. 15.3%, *P* = 0.01) [3]. Based on this study, PCI has been recommended for patients with limited-stage SCLC who have achieved a good response to chemoradiotherapy [2, 4].

However, the meta-analysis [3] has several limitations. The most important one is that no routine brain MRI was performed before PCI. A study conducted in the era of MRI demonstrated that 25% of newly diagnosed SCLC patients had brain metastasis (BM), and the cumulative incidence of BM after initial treatment could exceed 50% [5]. Our retrospective study showed that among all limited-stage SCLC patients who did not receive PCI and developed BM, 30.2% of them were detected before planned PCI with brain MRI [6]. Therefore, it can be speculated that some of the patients included in this meta-analysis actually received “treatment” rather than “prophylaxis”.

We have completed a prospective randomized study on the target volume of thoracic radiotherapy in limited-stage SCLC [7]. Our post-hoc analysis showed that, among 300 patients who received definitive chemoradiotherapy in this study, 134 (44.7%) achieved CR, 105 patients received PCI. All patients underwent baseline brain MRI, and 85.6% of them received brain MRI before PCI. The median follow-up time for the entire group was 22.3 months. Although PCI significantly reduced the incidence of BM (16.2% vs. 37.9%, *P* = 0.02), the median survival time for the PCI and the non-PCI arm were 30.2 months and 30.5 months, respectively, with 3-year OS rates of 39.9% and 43.0% (*P* = 0.93). PCI did not significantly improve the OS of patients who achieved CR after chemoradiotherapy. Among the 300 patients, 143 (47.7%) patients achieved partial remission (PR), of whom, 90 patients received PCI. Before PCI, 90.9% of patients received brain MRI. The median survival time for the PCI and the non-PCI arm were 27.4 months and 18.6 months, respectively, with 3-year OS rates of 42.6% and 17.4% (*P*<0.0001). PCI significantly improved the OS of patients who achieved PR after chemoradiotherapy (unpublished data).

Therefore, in the era of routine brain MRI surveillance, the role of PCI in limited-stage SCLC warrants further study. Based on above preliminary results, we speculate that PCI could be spared in patients who achieve CR after definitive chemoradiotherapy and instead, receive brain MRI surveillance. Even if BM is detected during follow-up, subsequent salvage treatment with SRS or whole-brain radiotherapy (WBRT) would not have a detrimental effect on OS.

## Methods

### Study design and objective

This is a prospective, randomized controlled study that includes patients with limited-stage SCLC who achieve CR after definitive chemoradiotherapy. Eligible patients will be randomly assigned to two arms:

Control arm: Patients receive PCI and regular brain MRI surveillance.Study arm: Patients receive regular brain MRI surveillance alone.

If BM is detected during follow-up, SRS is recommended when appropriate.

The primary endpoint is to compare the 2-year brain metastasis -free survival (BMFS) rates between the two arms. Secondary endpoints include 2-year OS, intra-cranial failure patterns, 2-year progression-free survival (PFS), cognitive functions(Hopkins Verbal Learning Test will be used to assess cognitive function).

### Key eligibility criteria

Inclusion criteria:

Histologically or cytologically confirmed small cell carcinoma.Age ≥ 18 years.Karnofsky Performance Status (KPS) ≥ 80.Limited-stage disease, defined as tumor confined to one side of the chest including ipsilateral lung, bilateral mediastinal lymph nodes, and bilateral supraclavicular lymph nodes (metastatic lymph nodes defined as short-axis diameter ≥ 1 cm or showing increased metabolic activity on PET-CT, or confirmed by mediastinoscopy / EBUS / TBNA biopsy). Pleural effusion thickness on chest CT is less than 1 cm (unless cytologically confirmed as malignant pleural effusion). Staging is determined according to the 8th edition of the AJCC staging system (2017), specifically stages I-IIIC without intrapulmonary metastasis.Have received curative-intent thoracic radiotherapy and chemotherapy.Assessment of treatment response within 4–6 weeks after completion of curative-intent thoracic chemoradiotherapy shows CR (evaluation includes contrast-enhanced chest and abdominal CT, contrast-enhanced brain MRI, whole-body bone scan, and lung cancer biomarkers such as NSE and ProGRP).Willingness and ability to comply with the follow-up schedule.Full understanding of the study and voluntary signing of an informed consent form.

Exclusion criteria:

History of malignant tumors in other parts of the body (previous or concurrent), excluding non-malignant melanoma, papillary carcinoma of the thyroid and cervical carcinoma in situ.Patients who have undergone curative surgery (excluding biopsy).Patients with a history of mental illness, in pregnancy or lactation.Uncontrolled diabetes, hypertension, or severe active infections.Manifested chronic central nervous system disorders.Contraindications for brain MRI examination.Other situations deemed unsuitable for enrollment by doctors in charge.

### Pre-treatment evaluation

Baseline staging include enhanced MRI of the brain, enhanced CT of the chest and upper abdomen, ultrasonography of the supraclavicular lymph nodes and bone scan. PET-CT is recommended, bone scan could be omitted if PET-CT is available. Laboratory tests include routine blood tests, routine liver and kidney function tests, lung cancer biomarker tests, electrocardiogram, echocardiography and pulmonary function test.

### Statistical analysis & sample size considerations

The study is designed as a prospective, randomized controlled non-inferiority trial. Based on previous study results, we hypothesize that the 2-year BMFS rate in the control group is 83%, and the 2-year BMFS in the study group is 68%, which is deemed acceptable as non-inferior. With a power of 80% and a one-sided significance level of 0.025, considering a shedding rate of 10%, 110 patients will be required in each group.

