### Tumor response evaluation criteria and definition of survival time

Tumor response will be evaluated according to Response Evaluation Criteria in Solid Tumors (RECIST) 1.1 criteria.

Brain metastasis-free survival (BMFS) is defined as the time from the start of treatment to BM or death from any cause. Progression-free survival (PFS) is defined as the time from the start of treatment to disease progression or death from any cause. Overall survival (OS) is defined as the time from the start of treatment to death from any cause.

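### The 83% control-arm 2-year BMFS behind the sample size is inconsistent with a BMFS that counts death and with the protocol's own survival data; on the protocol's own calculation, power would be about 56–59%, not 80%

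*Protocol article*

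**What the plan says.** Four places in the protocol article bear on this point.

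- Statistical analysis & sample size considerations, control rate: "we hypothesize that the 2-year BMFS rate in the control group is 83"%. The section attributes the assumption to earlier study results without naming the study.
- Same section. Non-inferiority level: "the 2-year BMFS in the study group is 68%, which is deemed acceptable as non-inferior". Error rates used for the calculation: "With a power of 80% and a one-sided significance level of 0.025". Resulting size after allowance for loss: "considering a shedding rate of 10%, 110 patients will be required in each group".
- Tumor response evaluation criteria and definition of survival time: "Brain metastasis-free survival (BMFS) is defined as the time from the start of treatment to BM or death from any cause". OS has the same time origin: "Overall survival (OS) is defined as the time from the start of treatment to death from any cause".
- Background, on the 134 complete responders of the sponsor's earlier randomized study, 105 of whom received PCI: "the median survival time for the PCI and the non-PCI arm were 30.2 months and 30.5 months, respectively, with 3-year OS rates of 39.9"% with PCI and 43.0% without. Incidence of brain metastasis was 16.2% with PCI and 37.9% without. Median follow-up of the whole group was 22.3 months.

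**The concern.** A patient who dies has had a BMFS event, so the BMFS curve lies on or below the OS curve at every time. An assumed 83% at 24 months therefore requires an OS of at least 83% at 24 months. The only survival figures the article gives for MRI-staged complete responders treated with PCI have half of them dead by 30.2 months.

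The assumed rate sets the variance in the sample size formula. The binomial variance p(1−p) is 0.141 at 83% and close to its maximum of 0.25 near 50–60%. If the true control rate is there, a 15-point margin cannot be tested with the stated power. The non-inferiority level also loses its meaning: 68% would lie above the rate to be expected in the PCI arm itself. The trial could then fail to show non-inferiority for lack of information alone.

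**Working it through.** **1. Reproduce the stated size.** Inputs from the sample size section: 83% in both arms, margin 83 − 68 = 15 points, one-sided alpha 0.025 (z = 1.960), power 80% (z = 0.8416), 10% loss.

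n = (1.960 + 0.8416)² × 2 × 0.83 × 0.17 / 0.15² = 98.4, so 99 evaluable per arm; 99/0.9 = 110. This is an exact match, and power at 99 is 80.2%. Other readings do not match: a superiority test of 83% against 68% needs 128 per arm before loss, and a non-inferiority formula using the 83%/68% variances needs 126. The calculation itself is sound; the question is its input.

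**2. Ceiling on control-arm BMFS.** Inputs from the Background, PCI-treated complete responders: S(30.2) = 0.50, S(36) = 0.399. Two-year OS under four assumed shapes:

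- Exponential through 3-year OS: 0.399^(24/36) = 0.542
- Exponential through the median: 0.5^(24/30.2) = 0.576
- Weibull through both points (shape 1.60): 0.5^((24/30.2)^1.60) = 0.619
- Hazard of months 30.2–36 extended back: ln(0.50/0.399)/5.8 = 0.0389 per month; 0.50 × exp(0.0389 × 6.2) = 0.636

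These are ceilings. Brain metastases in survivors lower BMFS further: as a rough illustration, 0.576 × (1 − 0.162) = 0.48.

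**3. What 83% would require.** With OS of 0.83 at month 24 and no brain metastases at all, the monthly hazard would be −ln(0.83)/24 = 0.008 up to month 24, then ln(0.83/0.50)/6.2 = 0.082 up to month 30.2, then 0.039 up to month 36.

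**4. Power on the protocol's own calculation.** Equal true rates p and a 15-point absolute margin: power = Φ(0.15/√(2p(1−p)/n) − 1.960). Example at p = 0.576, n = 99: the standard error is 0.0702; 0.15/0.0702 = 2.136; Φ(0.176) = 57.0%.

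| Control BMFS | Power, 99 evaluable | Power, 110 evaluable | Margin with 80% power, 99 evaluable | Enrolled per arm for 80% at 15 points |
|---|---|---|---|---|
| 83% | 80.2% | 84.2% | 15.0 | 110 |
| 63.6% | 59.2% | 63.8% | 19.2 | 180 |
| 57.6% | 57.0% | 61.4% | 19.7 | 190 |
| 50% | 56.0% | 60.4% | 19.9 | 195 |

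Margin column: 2.8016 × √(2p(1−p)/99). Last column: the formula of step 1, rounded up before and after division by 0.9.

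**5. Possible origin of the 83%.** 1 − 0.162 = 0.838. This is the crude proportion without brain metastasis in the earlier PCI-treated complete responders, and it does not count deaths.

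**6. Sensitivity to the margin scale.** Read as a hazard ratio, the margin is ln 0.68/ln 0.83 = 2.07. With d = 2 × 99 × (1 − p) events, power = Φ(½√d × ln 2.07 − 1.960): 56% at p = 0.83 (d = 34), 87% at 0.636 (d = 72) and 95% at 0.50 (d = 99).

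**The case against.** Several points count against a stronger statement, and most of them stand in part.

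- *A reader might infer that 83% is impossible.* The documents do not show this. No 2-year OS or BMFS is printed; the 54–64% is back-calculated from two later points with assumed curve shapes, in 105 patients, without confidence intervals. Sampling error is about ±9 points (1.96 × √(0.6 × 0.4/105)), which still does not reach 83%. The hazard pattern needed, a tenfold rise at month 24, is not credible but is not excluded by logic.
- *A reader might infer that the size was computed for a different endpoint.* That is only suggested. The sample size section does not name its source, 83.8% would round to 84%, and the matching figure without PCI is 62.1%, not 68%. The inconsistency does not depend on this explanation.
- *The new patients may do better.* Eligibility requires brain MRI at response assessment and KPS of at least 80, whereas 85.6% of the earlier complete responders had MRI before PCI. Using their survival as a ceiling is therefore an assumption. But even at a control BMFS of 70%, above every estimate here, the formula of step 4 gives 63% power, and at 75% it gives 68%. The time origin of the earlier survival figures is also unstated; if it lay before PCI, two years from PCI falls later on that curve and the ceiling is lower.
- *The power loss depends on the margin scale.* This stands. Under a hazard-ratio margin of 2.07, more events would raise power to about 87–95%. However, the article states rates, not a hazard ratio, and 110 reproduces on the absolute scale. On the hazard-ratio scale, 83% with 99 per arm would give only 56%.

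**Conclusion.** The assumed 83% is inconsistent with the endpoint definition and with the survival data in the same article. All three are in the current text, so this is not a detail left to an analysis plan. The plausible 2-year OS with PCI is about 54–64%, roughly 19–29 points below the assumed BMFS, and BMFS itself would be lower still.

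On the calculation that yields 110 per arm, the stated 80% becomes about 56–59% with 99 evaluable per arm, or 60–64% if nobody is lost. The 68% level exceeds every estimate of the PCI arm's own rate. These figures rest on three assumptions: the earlier cohort's survival carries over to this trial, the true rates are equal, and the 15-point absolute margin is kept at the lower rate. They are a conditional range, not a single established power. If a hazard-ratio margin was meant, the power is different and the protocol must state the margin on that scale.

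**What to change.** Reconcile the sample size section with the BMFS definition in one of two ways.

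(a) Keep BMFS with death as an event. Re-estimate the 2-year control rate on that definition from the sponsor's own complete responders. Then restate either the power at 110 per arm or the margin that 110 per arm can test with 80% power (about 19–20 points at a control rate of 50–64%), and say whether the margin is a difference in rates or a hazard ratio. Whether a wider margin is acceptable needs its own justification.

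(b) If freedom from brain metastasis was meant, redefine the primary endpoint as the 2-year cumulative incidence of brain metastasis with death as a competing event. Re-estimate the control value as a true 2-year cumulative incidence; the crude 16.2% at a median follow-up of 22.3 months for the whole group is not one. Restate the margin and power on that basis, and square the equal-rates assumption with the 37.9% incidence reported without PCI.

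The cost is protocol wording and one re-analysis of data the sponsor holds. The downside is a less favourable stated power under (a) or an amended endpoint definition under (b). Correcting the stated figure needs no additional patients; the 180–195 per arm in the working applies only if the sponsor chooses to keep both the 15-point margin and 80% power.

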Traditionally, WBRT is recommended for SCLC patients with BM. A recent large cohort study [11] compared the outcomes of SCLC patients with BM who received SRS or WBRT. The results showed that those treated with SRS had a median survival time of 8.5 months and a time to central nervous system progression (TTCP) of 8.1 months, while patients with a solitary BM treated with SRS had a median survival time of 11.0 months, and those treated with WBRT had a median survival time of 5.2 months. Although WBRT improved TTCP, it did not improve OS. Furthermore, after adjusting for prognostic factors, the OS results favored SRS.

Another study showed that in limited-stage SCLC patients who underwent MRI surveillance after definitive chemoradiotherapy, the occurrence of BM and survival rates did not significantly differ between patients who received SRS for detected BM and those who received PCI [12]. The survival benefit was attributed at least partially to SRS, reducing the contribution of PCI to survival. Although PCI is still recommended based on previous studies, these benefits may be diminished if MRI and SRS are available for diagnosis and treatment.

These findings challenge the traditional approach of using WBRT or PCI for all SCLC patients with BM and suggest that SRS guided by MRI surveillance could be a viable alternative in selected cases. However, it is important to consider individual patient factors, tumor characteristics, and treatment goals when determining the most appropriate management strategy.

Pezzi et al. [13] reported that in patients with limited-stage SCLC who had BM excluded by MRI were matched using a propensity score, although the 3-year incidence of BM was higher in the non-PCI group than in the PCI group, the difference was not statistically significant (20.4% vs. 11.2%, *P* = 0.10). Also, whether PCI was performed or not did not affect the overall survival (HR: 0.84, 95% CI: 0.604–1.180, *P* = 0.32).

Similarly, Qi et al. [14] conducted a retrospective matched analysis of 150 patients with limited-stage SCLC. The results showed a significantly lower 3-year cumulative incidence of BM in the PCI group compared to the non-PCI group (14.7% vs. 22.7%, *P* = 0.007), but there was no significant difference in median survival time between the two groups (35 months vs. 28 months, *P* = 0.128).

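### The 83% control rate behind the 15-point limit looks like a brain-metastasis-only figure, so meeting the limit on BM-or-death BMFS does not show that the BM excess is below 15 points

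*Protocol article*

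**What the plan says.** All references are to the protocol article. Under Statistical analysis & sample size considerations, the trial is a non-inferiority comparison of 2-year BMFS. Citing previous study results, it states "we hypothesize that the 2-year BMFS rate in the control group is 83" per cent and that "the 2-year BMFS in the study group is 68%, which is deemed acceptable as non-inferior". The test is planned "With a power of 80% and a one-sided significance level of 0.025", and "considering a shedding rate of 10%, 110 patients will be required in each group".

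The section on tumor response and survival definitions states: "Brain metastasis-free survival (BMFS) is defined as the time from the start of treatment to BM or death from any cause". Death is therefore an event.

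The Background gives the only earlier result that resembles the control rate, from complete responders in the sponsor's previous trial: "Although PCI significantly reduced the incidence of BM (16.2% vs. 37.9" per cent. Median survival in these patients was 30.2 months with PCI and 30.5 months without, and 3-year OS was 39.9% and 43.0%. The abstract's Discussion states the hypothesis that, for BM found during follow-up, "treatment with SRS or whole brain radiotherapy does not appear to have a detrimental effect on OS". On survival after BM, the main Discussion cites a cohort in which "those treated with SRS had a median survival time of 8.5 months".

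**The concern.** The limit is measured down from 83%. At that level, read as freedom from BM, almost every event is a BM, and 15 points means accepting 32% instead of 17% with BM. The endpoint tested also counts deaths. A patient who would have died by 2 years anyway is an event whether or not BM came first, so part of any BM excess disappears from the comparison. The dilution favours the MRI-only arm.

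The trial asks whether surveillance can replace PCI. A result that meets the BMFS limit could be read as showing brain control within 15 points of PCI when it has not shown that.

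**Working it through.** **1. The plan's own sample size.** With both arms truly at 83%, a margin of 0.15, one-sided 0.025 and 80% power: n = (1.960 + 0.842)² × 2 × 0.83 × 0.17 / 0.15² = 98.4, so 99 per arm, and 99/0.9 = 110. This matches. Reading 83% vs 68% as a difference to detect gives 128 per arm before dropout, which does not match. So 68% acts as the non-inferiority limit.

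**2. Can 83% be a BM-or-death rate?** By definition, BMFS at 2 years = OS at 2 years minus the proportion alive with prior BM, so BMFS ≤ OS. The article gives no 2-year OS. Assuming exponential survival:
- from the medians: 2^(−24/30.2) = 57.6%; 2^(−24/30.5) = 58.0%
- from 3-year OS: 0.399^(2/3) = 54.2%; 0.430^(2/3) = 57.0%

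83% lies well above all four. It does fit 100 − 16.2 = 83.8% BM-free. The 68% does not match 100 − 37.9 = 62.1%.

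**3. Pass probability.** With n = 99 per arm and Δ the true BMFS difference, pass = Φ((0.15 − Δ)/SE − 1.96), where SE = √[p₁(1−p₁)/99 + p₂(1−p₂)/99]. Checks: 83% vs 83% gives 80.2%; 83% vs 68% gives 2.5%.

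**4. BM 17% vs 32%, equal hazard of death without BM.** Let B and D be the 24-month cumulative hazards of BM and of death without BM. Then BMFS = exp(−(B+D)) and BM incidence = B/(B+D) × (1 − BMFS).

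Example with control BMFS 50%: B + D = 0.693, B = 0.17/0.50 × 0.693 = 0.236, D = 0.457. Keeping D = 0.457 in the MRI arm, an incidence of 32% needs B = 0.497, so BMFS = exp(−0.954) = 38.5%. Then Δ = 11.5 points, SE = 0.0701 and pass = Φ(0.50 − 1.96) = 7.2%.

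| Control BMFS | MRI BMFS | Difference (points) | Pass |
|---|---|---|---|
| 45% | 34.2% | 10.8 | 8.8% |
| 50% | 38.5% | 11.5 | 7.2% |
| 55% | 42.9% | 12.1 | 6.1% |
| 60% | 47.3% | 12.7 | 5.2% |

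Control BMFS is an assumption; 60% is generous against the OS in step 2. Widening the inputs to control-arm 2-year OS of 50-70% and post-BM medians of 5.2-18 months gives about 4-12%.

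**5. Same BM excess, OS forced equal.** Only BM patients alive at 24 months now separate the arms. With BM spread evenly over 24 months and a post-BM median of 8.5 months, k = ln 2/8.5 = 0.0815, and the fraction alive is f = (1 − e^(−24k))/(24k) = 0.439. So Δ = 0.439 × 15 = 6.6 points. At OS 58%, BMFS is 50.5% vs 44.0% and the pass rate is 22.0%; it is much the same for OS of 54-64%. The article's other medians give about 18% (11.0 months, solitary BM treated with SRS) and 32% (5.2 months, WBRT).

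This model needs death without BM to be 1 − 0.505 − 0.17 = 32% with PCI but 1 − 0.440 − 0.32 = 24% with MRI alone.

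**6. Power on the composite scale.** If both arms are truly at 50%, SE = 0.0711 and power is Φ(0.15/0.0711 − 1.96) = 56%, not 80%.

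**The case against.** The strongest reply is that the article calls both rates BMFS and never says they are BM-only. The match to 83.8% is an inference, and that figure is a crude incidence (median follow-up 22.3 months for the whole group), not a 2-year rate. The 68%, which fixes the margin, matches nothing and is a judgement. This stands: the text does not support saying that both rates were taken from the BM-only scale. What survives is that 83% is not credible as a BM-or-death rate beside the article's own survival data.

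A reader might infer that the type I error is inflated to 5-22%. It is not. For a true 15-point BMFS deficit the error remains 2.5%. The higher figures are the chance of passing when the excess in BM alone is 15 points, a quantity for which the article sets no separate limit. That a composite with death is less sensitive to one component is a general property of such endpoints.

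A reader might also take 22% as the expected size. It needs equal OS although 15 points more patients develop BM and then survive a median of 8.5 months, which requires clearly fewer deaths without BM in the MRI arm. The article hypothesises no OS detriment but reports no such effect on other deaths. The 8.5 months comes from a cohort of SCLC patients with BM, not described as limited-stage complete responders under three-monthly MRI.

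Finally, intra-cranial failure patterns and OS are secondary endpoints, so readers will see the components, and a competing-risk estimate could be in an analysis plan that is not shown. That softens the point. It does not reconcile a control rate and an endpoint definition that the article itself states and that do not fit together.

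**Conclusion.** The point holds in a limited form. The control rate from which the limit is measured appears to be on a BM-only scale, while the endpoint counts death. A true 15-point BM excess would show as about 11-13 BMFS points and pass in about 5-9% of trials, assuming an equal hazard of death without BM, control BMFS of 45-60% and 99 evaluable per arm. About 22% is reached only under equal OS with an 8.5-month post-BM median. Meeting the BMFS limit therefore does not establish that the BM excess is below 15 points. Power is affected by the same mismatch: about 56% instead of 80% if both arms are near 50%. Confidence is moderate, because the origin of 83% is inferred and 2-year OS is read from medians and 3-year rates.

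**What to change.** In the statistical section:

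1. State where 83% and 68% come from, and restate the control rate, the limit and the resulting power on the BM-or-death scale.
2. Pre-specify the 2-year cumulative incidence of BM in each arm with death without BM as a competing event (Aalen-Johansen), and the 95% confidence interval of the difference.
3. State that a non-inferiority conclusion applies to BMFS only, and that non-inferior brain-metastasis control will not be claimed unless the upper limit of that interval is also below 15 points.

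The cost is one extra analysis, a less favourable stated power, and a narrower claim from BMFS alone. No new data or patients are needed for these changes, since MRI findings and deaths are already followed for 2 years. Restoring 80% power at 15 points would be a separate decision: near 50% BMFS it needs about 175 evaluable, or 175/0.9 ≈ 195 enrolled, per arm.

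The claim about brain control becomes harder to reach. In simulation with equal arms (BM 17%, BMFS 50%), the BMFS limit is met in about 58% of trials (56% by the normal approximation) and both conditions in about 52%. At BM 17% vs 32% with equal hazard of death without BM, requiring both lowers the chance of that claim from about 8% to about 1%. Making the BM condition a second mandatory criterion for the trial's primary result would go further and is a debatable trade-off; limiting the claim is enough.
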